### **Statistical methods**

Continuous variables will be analysed by Student’s t test for independent samples, or repeated measures ANOVA for multiple measurements over time. The primary endpoint will be assessed using Fisher’s exact test. Recovery profiles over time will be tested using the Cochran Mantel Haenzel test for repeated measurement of proportions, and will test the global hypothesis for difference between groups over time.

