### **Study design**

Parallel randomized trial with allocation ration 1:1.

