### **Outcome measurements for both studies**

**Primary outcome**:

Quality of recovery, as measured by the postoperative quality recovery scale (PQRS) at Day 3 for recovery in all of the individual recovery domains (all domains recovery).

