### **Study size**

Sample-size estimates are based on the pilot data for all domains recovery at day 3 (desflurane 35.2% vs sevoflurane 20%) and using Fisher’s exact method to determine a difference of 10% difference in the total score using a 2-tailed test with 80% power at a *P*=0.05 significance. The minimal sample size is 137 for each group. This will be increased to 150 patients per group to account for potential non-completions.

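### Fisher's exact test for the primary endpoint is valid but conservative, and costs 2.4 points of power at 150 per arm and 3.3 at 137

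*Protocol*

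**What the plan says.** The primary outcome (Protocol, Primary outcome) is PQRS recovery "at Day 3 for recovery in all of the individual recovery domains (all domains recovery"), so each patient either has or has not recovered. Allocation is 1:1 (Study design: "Parallel randomized trial with allocation ration 1:1"). Statistical methods fixes the test: "The primary endpoint will be assessed using Fisher’s exact test".

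Study size names the same Fisher method for the calculation. It takes the pilot rates of 35.2% (desflurane) and 20% (sevoflurane) as its basis, "using a 2-tailed test with 80% power at a *P*=0.05 significance". It then says "The minimal sample size is 137 for each group" and "This will be increased to 150 patients per group to account for potential non-completions". The same sentence as the pilot rates also gives the aim as "to determine a difference of 10% difference in the total score", which does not match the 15.2-point gap between those rates.

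**The concern.** Fisher's test conditions on the total number recovered. Because the conditional distribution is discrete, its true error lies below the nominal 5%, and some of that gap is visible even with 137 to 150 patients per arm. An exact unconditional test can use most of the unused allowance without exceeding 5%.

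At stake is a little power on the only primary comparison. It matters mainly because Study size treats 137 as sufficient and the other 13 per group as cover for non-completion. If the named test does not deliver 80% at 137, the allowance does not do what it is there for.

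**Working it through.** **Inputs.** p1 = 0.352, p2 = 0.20, two-sided 0.05, 80% power, n = 137 and 150 per arm (all from Study size), 1:1 allocation (Study design). The common rate under the null is taken as (0.352 + 0.20)/2 = 0.276.

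**The plan's own figure.** The pooled normal approximation without continuity correction is

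n = [1.960·√(2·0.276·0.724) + 0.842·√(0.352·0.648 + 0.20·0.80)]² / 0.152² = (1.239 + 0.524)² / 0.0231 ≈ 135.

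With 35% versus 20% it gives 138. The stated 137 is therefore close to an uncorrected normal approximation. With continuity correction, 35.2% versus 20% gives 148. Full enumeration of Fisher's test gives 147 (146 gives 79.9%, 147 gives 80.2%).

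**Fisher's test.** Let R be the set of tables (x, y) with two-sided Fisher P ≤ 0.05, and b the binomial probability.
- Size(π) = Σ over R of b(x; n, π)·b(y; n, π)
- Power = Σ over R of b(x; n, 0.352)·b(y; n, 0.20)

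**Boschloo's test.** The statistic is the Fisher P value. The cut-off c is the largest value for which the size, maximised over the common rate (500-point grid from 0.001 to 0.5; higher rates follow by symmetry), is at most 0.05. This gives c = 0.0642 at n = 137 and 0.0616 at n = 150. Both exceed 0.05, so every table that Fisher's test rejects is also rejected by Boschloo's.

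| | n = 137 Fisher | n = 137 Boschloo | n = 150 Fisher | n = 150 Boschloo |
|---|---|---|---|---|
| Size at 27.6% | 3.65% | 4.8% | 3.75% | 4.7% |
| Maximum size over common rates | 3.9% | 4.99% | 4.3% | 4.95% |
| Power, 35.2% vs 20% | 77.2% | 80.5% | 81.3% | 83.7% |
| Power, 30% vs 20% | 42.8% | 47.3% | 46.9% | 50.6% |

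Differences in power for 35.2% versus 20%: 80.5 − 77.2 = 3.3 points at 137, and 83.7 − 81.3 = 2.4 points at 150.

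**Between these sizes.** The same enumeration was run at every n from 136 to 150. Boschloo's power is at least 80% throughout (80.1% at 136). The gain over Fisher's test is not smooth: it runs from 3.4 points at 136 down to 1.7 at 142 and back to 2.4 at 150. In patients, 80% power needs 136 completers per arm with Boschloo's test and 147 with Fisher's, a difference of 11.

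**Sensitivity.**
- Fisher's true size ranges from about 3.1% to 4.3% for common rates from 10% to 50%.
- If the desflurane rate is rounded to 35%, power at 137 is 76.1% with Fisher's test and 79.5% with Boschloo's. At 150 it is 80.3% and 82.8%.

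**The case against.** The protocol contradicts nothing on this point. Study size and Statistical methods name the same method, which is prespecified, standard and valid. That stands.

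Three stronger readings are tempting, and the document supports none of them.

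- **That the trial runs at the wrong error rate.** A reader might set 3.7% against 5% and see a breach. The 0.05 in Study size is a significance threshold, so it is an upper limit. Fisher's test respects it, and the departure is on the safe side.
- **That Fisher's test is the wrong test because the number recovered is not fixed by design.** This is contested. Under the sharp null in a randomised trial, each patient's outcome is the same in either arm. The total recovered is then fixed, and with arm sizes held fixed Fisher's test is the randomisation test. Boschloo's test assumes two independent binomial samples. Either model can be defended.
- **That the protocol is deficient because it gives no confidence interval for the primary comparison.** Reporting of intervals is commonly left to the statistical analysis plan, which is not shown here. That is not a finding.

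It is also fair to say that the shortfall at 137 comes partly from the sample-size calculation: 137 fits a normal approximation better than the Fisher method it is attributed to. With 147 or more evaluable per arm, Fisher's test reaches 80% without any change. What remains is that, with the numbers as planned, the choice of test decides whether 80% is met when between 136 and 146 patients per arm are evaluable.

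**Conclusion.** The point holds as a minor, cheap efficiency gain. Fisher's test is valid here, but at 35.2% versus 20% it gives up 2.4 points of power with 150 evaluable per arm and 3.3 with 137. At the protocol's own minimum it gives 77.2%, below the stated 80%, where Boschloo's test gives 80.5%. With Fisher's test the allowance for non-completion covers 150 − 147 = 3 losses per arm, against the 150 − 137 = 13 intended. With Boschloo's test it covers all 13.

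This rests on the planning rates being right, on equal numbers of completers per arm and on two independent binomial samples. Meeting 80% at 137 is a narrow matter: with 35% in place of 35.2%, Boschloo's test gives 79.5% there. The advantage over Fisher's test is steadier than that crossing, but its size varies with n.

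The change does not touch the larger difficulty in Study size, the stated 10% difference. For 30% versus 20% at 150 per arm, power is about 47% with Fisher's test and 51% with Boschloo's.

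**What to change.** Before unblinding, replace the sentence in Statistical methods with wording such as: The primary endpoint will be compared between groups with Boschloo's exact unconditional test at a two-sided 5% level; Fisher's exact P value will be shown alongside for reference. Name the same test in Study size and restate the calculation for it (136 completers per group for 80% power at 35.2% versus 20%). Say plainly that Boschloo's result is the primary one, so that there is no choice between two P values.

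If Fisher's test is kept, correct Study size to say that 147 completers per group are needed for 80% power, and review whether 150 recruited leaves enough room for losses.

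The cost is two short edits and a rerun of the sample-size calculation, with no extra patients or visits. The downsides are a test less familiar to clinical readers and a true error at the planning rates that rises from about 3.7% to 4.7% (at 150 per arm), still within 5%.

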However, we conducted a pilot study arm with sevoflurane as the general anaesthetic agent. We recruited 10 patients in each of the young and older cohorts. Other aspects of the study conduct were identical to the patients receiving desflurane anaesthesia. In brief, Patients were induced with propofol, and maintained on wither desflurane or sevoflurane according to allocation. Intraoperative and postoperative opiates were used for analgesia. Nitrous oxide anaesthesia was not used. Patients were typically discharge on the same day of surgery. PQRS measurements were performed at Baseline n the day of surgery, 15 and 40 minutes, 1 and 3 days, and 3 months after the end of anaesthesia.

Pilot study results:

Due to the small numbers in each of the young and old groups in the sevoflurane arms, all patients were combined to compare the recovery profiles of desflurane and sevoflurane. However, the proportion of patients in young and old ages were the same for both anaesthetics. 122 patients are included in the desflurane group and 20 in the sevoflurane group.

The figure below shows recovery between groups for all domains, as well as the individual recovery domains.

The P value displayed is derived using the Cochran Mantel Haenzel test for repeated

measurement of proportions, and tests the global hypothesis of whether a difference exists in the recovery profiles over time between the two agents. P<0.05 was used to define significance.

Caution must be exercised in interpreting the P value, due to the small n in the sevofluane group compared to the desflurane, and there is high chance of Type II error where there is a P>0.05. Rather, place emphasis on the presence of absence of differences in the recovery profiles, as an indicator of effect size.

*A. Physiological recovery domain for Time 15 and 40 minutes. B. Cognitive recovery profile using the revised cognition scoring method. C. Nociceptive domain includes pain and nausea. D. ADL is activities of daily living and tests the ability to eat, walk, stand and dress. E. Emotive recovery tests feelings of anxiety and depression. F. Overall recovery is present when there is recovery on all of the domains (A-E).*

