**Study assessments protocol**

Patients will be recruited prior to but on the same day as surgery. Baseline measurements using the PQRS will be performed prior to premedication.

Measurements will then be performed using the PQRS battery at 15 minutes, 40 minutes, one day, three days and three months following surgery. This is the same testing paradigm as we have used in the validation study of the PQRS. Whilst in hospital, testing will be conducted face-to-face, whereas following discharge from hospital; these will be conducted via telephone interview.

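### The Cochran-Mantel-Haenszel test of recovery profiles treats repeated measurements on the same patients as independent, so its type I error exceeds 5% if a patient's outcomes are positively correlated

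*Protocol*

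**What the plan says.** The Statistical methods section assigns the primary endpoint to Fisher's exact test and gives a separate method for the course of recovery: "Recovery profiles over time will be tested using the Cochran Mantel Haenzel test for repeated measurement of proportions". It adds that this test "will test the global hypothesis for difference between groups over time".

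The Study assessments protocol sets the repeated measurements: "Measurements will then be performed using the PQRS battery at 15 minutes, 40 minutes, one day, three days and three months following surgery". The Study design section describes a parallel trial with 1:1 allocation. Secondary outcomes are recovery in all domains and within each domain at the various times.

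The same test was used for the pilot data (under Clinical significance), where it "tests the global hypothesis of whether a difference exists in the recovery profiles over time between the two agents". The choice is therefore deliberate. The protocol names no clustered variance, and no model for correlated binary data.

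**The concern.** The Cochran-Mantel-Haenszel (CMH) statistic sums observed-minus-expected counts over a set of 2x2 tables and divides by the sum of the table variances. That sum is the right variance only if the tables are independent. Tables for successive times on the same patients are not. Positive correlation is the natural expectation, because the Background defines recovery broadly as a return to the patient's own baseline or better: an unusually poor baseline makes recovery easier at every later time. This is an inference; the protocol reports no correlation.

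At stake are the claims about recovery over time, overall and by domain. If P values are too small, the trial may report that one agent gives better recovery in some domain when the two do not differ. The Clinical significance section expects the results to guide the choice of agent, so such a claim would matter.

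**Working it through.** **Inputs**

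- Arms and size: two arms, 1:1, 150 per group planned (Study design; Study size).
- Number of times T: five (Study assessments protocol). The pilot figure legend shows "Physiological recovery domain for Time 15 and 40 minutes", so T = 2 for that domain if the trial does the same. T = 4 is included for a domain that omits one time.
- Nominal level: two-sided 5%. The sample size was set "using a 2-tailed test with 80% power at a *P*=0.05 significance", and for the pilot CMH tests "P<0.05 was used to define significance". No separate level is given for the profile tests.
- Mean within-patient correlation ρ between binary outcomes at different times: not in the protocol. Assumed range 0.05 to 0.5.

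**Step 1: which stratum?** The variance of one table is V = n₁n₀m(N−m)/(N²(N−1)), where n₁ and n₀ are the numbers on each agent, m the number recovered and N the total. If the patient is the stratum, every table has n₁ = 0 or n₀ = 0, so V = 0 and the table says nothing about the agents. Time is the only stratum under which the test can compare them.

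**Step 2: true variance.** With T time strata of similar variance V, CMH divides by T·V. With the same patients in every stratum, the variance of the sum is about T·V·(1 + (T−1)ρ). The true two-sided error of a nominal 5% test is therefore

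α = 2·[1 − Φ(1.96/√(1 + (T−1)ρ))].

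**Step 3: numbers**

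| T | ρ | 1 + (T−1)ρ | True error |
|---|---|---|---|
| 5 | 0 | 1.0 | 5.0% |
| 5 | 0.05 | 1.2 | 7.4% |
| 5 | 0.1 | 1.4 | 9.8% |
| 5 | 0.3 | 2.2 | 18.6% |
| 5 | 0.5 | 3.0 | 25.8% |
| 4 | 0.1 | 1.3 | 8.6% |
| 4 | 0.5 | 2.5 | 21.5% |
| 2 | 0.1 | 1.1 | 6.2% |
| 2 | 0.5 | 1.5 | 10.9% |

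**Step 4: simulation.** Correlated binary outcomes were generated from a latent normal model with no difference between agents: 150 per arm, 20,000 trials per scenario, three assumed recovery profiles. CMH was applied with five time strata.

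| Mean binary correlation | Simulated error |
|---|---|
| 0 | 4.8–5.2% |
| 0.07–0.09 | 8–9% |
| 0.14–0.18 | 12–14% |
| 0.25–0.32 | 16–19% |
| 0.36–0.48 | 20–25% |

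A continuity correction lowers these by about 1 percentage point. Correlation that decays with time gives the same answer at the same mean. One such scenario had mean correlation 0.157 and simulated error 12.5%; the formula has 1 + 4 × 0.157 = 1.628, which also gives about 12.5%.

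**Step 5: is clustering the cause?** Keeping the CMH numerator and replacing its denominator by the variance of each patient's total over the five times gave an error of 4.9% to 5.3% in every five-time scenario. Ignoring the clustering accounts for the excess.

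**The case against.** The strongest reply is that the damage is limited. The primary endpoint and the sample size both rest on day 3 proportions, not on CMH. This stands, and it settles the severity: a reader might infer that the trial's main conclusion is at risk, and the protocol does not support that.

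Second, a reader might take a single inflated error rate as established. It is not, because the protocol gives no correlation. Correlation may also fade between 15 minutes and three months. In simulations with one assumed profile, decaying latent correlations of 0.2, 0.3 and 0.5 between adjacent visits gave errors of about 8%, 10% and 13%, against about 10%, 13% and 17% when the correlation was constant. The upper end of the range needs a mean correlation of about 0.4 or more, which nothing in the protocol supports directly. The direction of the error remains.

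Third, one might say that the test is wrong because it misses profiles that cross. Differences of +15 points at two early times and −15 at two later times do cancel: at zero correlation the test rejects only about 5% of the time. But the wording in Statistical methods can be read as an average difference over time, and the background and pilot data mostly favour desflurane rather than predicting a reversal. This is a limitation of the test, to be settled by naming the hypothesis, and not a proven error.

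Fourth, the phrase about repeated measurement might be thought to imply a correction. None is stated. A statistical analysis plan could replace the test, but the protocol names it outright and has not merely left a detail open.

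Finally, a reader might extend the point to the repeated-measures ANOVA in the same section. That line concerns continuous variables and does not say how missed visits are handled, so it gives no ground for this criticism.

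**Conclusion.** The concern holds for the secondary profile analyses and should be corrected before analysis. As written, the test rejects too often whenever outcomes within a patient are positively correlated. For an assumed mean correlation of 0.05 to 0.5, the true error is about 7% to 26% with five times. For 0.1 to 0.5 it is about 9% to 22% with four times and about 6% to 11% with two. The two-time figure applies to the physiological domain if it is measured only at 15 and 40 minutes.

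These figures rest on time being the stratum, which is inferred but is the only workable reading, and on the correlation, which is assumed. The pilot P values come from the same test and share the weakness. No design figure depends on them, and the pilot text already urges caution, although because of the small sevoflurane group.

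**What to change.** Replace the CMH test in Statistical methods with an analysis clustered on patient, such as a logistic GEE with robust standard errors and terms for agent and time. For each domain, use only the times at which that domain is measured.

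State in advance which hypothesis is the global test:

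- the average agent effect over time, with one degree of freedom, which is closest to what CMH addresses; or
- the joint test of agent and agent-by-time, if a difference in profiles is meant to include differences that change direction.

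The cost is a change of wording and a standard procedure, with no new patients or data. Some secondary P values will be larger. The joint test also loses power against a consistent difference: in a simulation of a steady 8-point benefit at five times with latent correlation 0.3, the clustered one-degree test had about 75% power and the five-degree joint test about 56%. That trade-off is a reason to fix the choice before the data are seen.

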### **Ethical issues**

This study will be reviewed by the Epworth HealthCare HREC. All patients will receive a written plain language statement and will provide informed written consent.

Both desflurane and sevoflurane are commonly used general anaesthetics in Australia. If the participating anaesthetist believes that the anaesthetic regimen is inappropriate, or that the patient requests regional anaesthesia, then the patient will not be recruited into the study. Each PQRS measurement takes approximately 5-10 minutes, and is not onerous or stressful to the patient. However, if the patient does not wish to participate further, then they may withdraw from the study. Measurements performed after discharge from hospital are conducted via telephone interviews and do not require the patient to return to the hospital or other location. The interviews are arranged between the researcher and patient at a time of mutual convenience.

### **Randomization**

The randomization sequence will by produced using a computer generated randomization sequence. Concealment will be by placing the card containing the allocation information in double opaque sealed envelopes, and concealment will be maintained until after recruitment and the patients is admitted into the operating theatre. The treating anaesthetist will then open the envelopes to reveal the allocation. A non-participant in any process of the study will perform preparation of the envelopes. A copy of the randomization sequence will be stored in a separate databank, which is password protected and not available to the investigators until the study is complete.

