### **Interventions**

**Common management for both groups wil include the following:**

1. Pre-medication other than oral analgesic (such as paracetamol) will not be used.

2. Induction will be with intravenous propofol, including co-induction consisting of fentanyl 25-100 micrograms and midazolam 1-5 mg. Antimemetics including dexamethasone and 5HT_3_ antagnists (such as ondensetron) may be administered by the treating anaesthetist.

3. Analgesia will consist of intraoperative opiates, 1 g paracetamol qid, intravenous opiates during early recovery (such as 1.v. fentanyl), Morphine 2.5-10mg sc 3 hourly, or oxynorm 10-20mg 6 hourly will be used for breakthrough analgesia. NSAID’s including Cox II inhibitors (such as paracoxib 40mg i.v. amy be used.

4. Patients will not be included in the study if the treating anaesthetist considers that a regional anaesthetic rather than a general anaesthetic would be in the best interest of the patient. This would most likely be a spinal anaesthetic.

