**Intervention drug.**

Following induction of general anaesthesia either desflurane or sevoflurane will be introduced as the maintenance anaesthetic and titrated to maintain an adequate clinical depth of anaesthesia for the remainder of the operation. Typically this will involve anaesthetic concentrations of 6% desflurane and 2.4% sevoflurane, reflecting the different potencies of the drugs. If Bispectral index monitoring (depth of anaesthesia monitor) is available, the target range is 40-60.

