### **Blinding**

Due to the nature of the drugs, it is not possible to blind the treating anaesthetist to the allocation, but the patient and study investigators who collect the PQRS data will be blinded to allocation.

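### The envelope may be opened before induction, so the unblinded anaesthetist can choose co-induction drugs and antiemetics knowing the arm, although the study agent is introduced only after induction

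*Protocol*

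**What the plan says.** Four parts of the protocol bear on the order of events in theatre.

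- **Randomization:** "concealment will be maintained until after recruitment and the patients is admitted into the operating theatre. The treating anaesthetist will then open the envelopes", which disclose the arm.
- **Blinding:** "it is not possible to blind the treating anaesthetist to the allocation". Patients and the investigators who collect the PQRS are to be blinded.
- **Interventions, common management, item 2:** "Induction will be with intravenous propofol, including co-induction consisting of fentanyl 25-100 micrograms and midazolam 1-5 mg". Dexamethasone and 5HT3 antagonists "may be administered by the treating anaesthetist". Item 1 rules out premedication other than oral analgesia, so midazolam belongs to induction.
- **Intervention drug:** "Following induction of general anaesthesia either desflurane or sevoflurane will be introduced as the maintenance anaesthetic".

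The primary outcome is PQRS recovery in all domains at Day 3. The secondary outcomes include each domain at 15 minutes, 40 minutes, day 1, day 3 and 3 months. Cognition is one domain; the nociceptive domain covers pain and nausea.

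**The concern.** Someone who knows the arm can choose sedative, opioid and antiemetic treatment differently in the two arms. Any resulting difference in recovery would be credited to the volatile agent. Blinding the patient and the assessor guards against biased reporting and scoring, but not against a real difference in treatment received.

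The protocol itself supplies expectations that could prompt such choices. The Background describes faster emergence with desflurane, more variable recovery times with sevoflurane, and airway irritation with desflurane at high concentration. The pilot results report better nociceptive recovery with desflurane, and day 1 cognitive recovery of 78% against 56%. An anaesthetist might compensate in either arm, so the bias could dilute a true difference or create a false one.

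The exposure is partly avoidable. Blinding the anaesthetist is impossible once the agent is running, but not while the co-induction drugs are being chosen.

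**Working it through.** **1. Order of events, with the sections side by side.**

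| Step | Section | Allocation known to the anaesthetist? |
|---|---|---|
| Recruitment and baseline PQRS | Study assessments protocol; Randomization | No |
| Patient enters theatre, envelope then opened | Randomization | Yes, from here |
| Propofol, fentanyl, midazolam; antiemetics optional | Interventions, item 2 | Yes, on the plain reading |
| Desflurane or sevoflurane introduced | Intervention drug | Yes, necessarily |
| Intraoperative and recovery analgesia | Interventions, item 3 | Yes; timing of opening cannot change this |

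The third row is the avoidable one. No section ties the opening to the end of induction, sets these choices by a rule, or asks for them to be recorded before opening.

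**2. Width of the discretion.** The ranges are given in "including co-induction consisting of fentanyl 25-100 micrograms and midazolam 1-5 mg". Fentanyl: 100/25 = 4-fold. Midazolam: 5/1 = 5-fold. Antiemetics: given or not given.

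**3. Size.** The protocol gives no figure for this bias, so there is none to reproduce. It reports neither how co-treatment differs by arm nor how it affects the PQRS. The following is an illustration only. If a co-treatment changes the probability of all-domains recovery by e, and its use differs between arms by u, then

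bias in the arm difference = u × e.

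Assumptions: no true agent effect; mean recovery (35.2% + 20%)/2 = 27.6%, from the planning rates under Study size; 150 per group; two-sided Fisher's exact test at 0.05; e = 10 to 15 points; u = 10 to 30 points. The values of e and u are not in the documents.

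| u (points) | Bias for e = 10 to 15 (points) | Fisher rejection rate |
|---|---|---|
| 0 | 0 | 3.7% |
| 10 | 0.10 × 10 = 1.0 to 0.10 × 15 = 1.5 | 4.1% to 4.6% |
| 20 | 0.20 × 10 = 2.0 to 0.20 × 15 = 3.0 | 5.2% to 7.1% |
| 30 | 0.30 × 10 = 3.0 to 0.30 × 15 = 4.5 | 7.1% to 11.5% |

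Under these inputs the false-positive rate stays below 5% at a 10-point imbalance and exceeds it at 20 points or more. The assumed e is generous for Day 3: it is close to the whole pilot difference between agents, 35.2 − 20 = 15.2 points.

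**The case against.** Several objections are fair, and they limit the point.

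- **The timing is inferred.** The Randomization section never mentions induction. It fixes the earliest moment of opening, and opening just after induction would also fit the words. This stands: the protocol does not state that opening precedes induction. Immediate opening remains the natural reading, and the later moment is nowhere required.
- **Day 3 is remote from induction.** That these drugs affect cognition and nausea is general pharmacology, not something the protocol shows, and any effect is likely to be larger at 15 and 40 minutes than at Day 3. This stands too. The early time points are secondary, and a reader should not infer that bias in the primary outcome has been shown.
- **The illustration rests on assumptions.** Stating the bias as a share of the pilot difference would only restate the chosen inputs, so it is no evidence of size.
- **Safeguards exist.** Management is described as common to both groups, and patients and assessors are blinded. But common ranges do not secure common treatment when the person choosing within them knows the arm.
- **The remedy is partial.** The anaesthetist must know the agent during maintenance, so later choices remain open. This stands and belongs in the recommendation.

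A reader might also infer selection bias: that a switch to regional anaesthesia could be decided with the allocation known. The documents do not support this. Interventions item 4 and Ethical issues make a preference for regional anaesthesia a reason not to recruit, and concealment lasts until after recruitment. Nothing here calls allocation concealment into question.

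**Conclusion.** The concern holds as a weakness of sequence. On its plain reading the protocol reveals the allocation to an anaesthetist who cannot be blinded, before that person makes discretionary choices that do not depend on knowing the agent. The protocol shows that co-treatment can differ by arm, not that it will. The result is an avoidable opportunity for performance bias in either direction, most plausible for the cognitive and nociceptive domains at 15 minutes, 40 minutes and day 1, and possible for the Day 3 primary outcome because failure in one domain is failure overall. Its size is unknown; the table above is conditional on its inputs and suggests a small effect unless the imbalance is large. It is worth correcting because the change is cheap, and because treatment chosen with the arm known cannot be undone afterwards.

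**What to change.** Amend the Randomization section so that the treating anaesthetist opens the envelope only after induction is complete and the intended antiemetic and analgesic plan has been written on the case form. Record the co-treatments actually given, and report them by arm.

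No drug or range needs to change. The cost is a different order of steps in theatre, a line on the case form, and having both agents ready at induction. The change protects the co-induction doses and any antiemetic already given. The written plan does not bind later choices, but it lets departures from it be seen by arm. Intraoperative opioids, later antiemetics and recovery analgesia will still be chosen with the allocation known, and the trial report should say so.
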